##### Hearing test

2.6.1.6

The hearing test will be conducted using an automated application to ensure accuracy and reliability. The testing environment will require ambient noise to be <40 dB. The “Hearing Bao” APP will be used to test both the left and right ears, and ambient noise levels will be recorded. The test will include frequencies of 125 Hz, 250 Hz, 500 Hz, 1,000 Hz, 2000 Hz, 4,000 Hz, and 8,000 Hz. However, for analysis, only the data from the WHO-recommended frequencies of 500 Hz, 1,000 Hz, 2000 Hz, and 4,000 Hz will be used. According to the standards, if the hearing test result for any ear in these four frequencies is ≤35 dB, the hearing function for that ear will be considered normal. Hearing function will be considered normal only when the test results for both ears are normal across all four frequencies.

##### Patient health Questionnaire-9

2.6.1.7

The PHQ-9 (38) contains nine items, including loss of pleasure, low mood, sleep difficulties, lack of energy, eating disorders, low self-esteem, concentration difficulties, slow movement, and self-harm/suicidal ideas. These items use a 4-point Likert scale, ranging from “not at all” to “nearly every day.” The total score ranges from 0 to 7, with a higher score indicating a higher severity. This scale had a satisfactory Cronbach’s *α* coefficient among students (39) and the internal consistency of the scale was also good.

##### Adherence, adverse events, and satisfaction

2.6.1.8

In the empirical study of long-term care intervention program based on ICOPE for old patients with disabilities in nursing homes, adherence, adverse events, and satisfaction are key indicators for evaluating the intervention’s effectiveness. Adherence reflects the degree to which participants follow the prescribed intervention, including the frequency and duration of their participation. Adverse events are any untoward medical occurrences in a participant during a clinical trial. To ensure participant safety, a response protocol will be implemented. If a participant becomes distressed or unwell and cannot attend a session, it will be rescheduled based on their condition. Participants will be closely monitored by nursing home staff and the research team, with timely medical support provided as needed. The intervention will be paused if continued participation poses a risk, and clinical assessment will be arranged if necessary. All adverse events will be documented and reported to the ethics committee. Satisfaction will be assessed to capture participants’ subjective experiences, perceived benefits, and attitudes toward the intervention, which is critical for evaluating the intervention program’s acceptability and for informing future improvements.

#### Qualitative data collection

2.6.2

The old patients with disabilities in nursing homes who have completed the 12-week “long-term care intervention program based on ICOPE for old patients with disabilities in nursing homes” will be invited to participate in focus group interviews to explore their experiences of taking part in the intervention. Table 3 shows the details of the interview outline.

**Table 3 tab3:** Semi-structured interview outline.

Number	Questions
1	What were the main reasons you initially enrolled in this program? Please explain and rank them by importance.
2	How did you feel and what were your experiences after participating in this care intervention program?
3	What challenges did you encounter during the implementation of this care intervention program? What was the biggest challenge? How was it resolved? Please provide an example.
4	Would you be willing to continue participating in this care program in the future? Would you recommend this program to others around you? Please explain.
5	How do you think this care intervention program benefits you compared to traditional care models?
6	What kind of help and support would you like to receive in the future at the nursing home? Are there any areas that need improvement or further development? Please explain.
7	Is there anything else you would like to add to today’s conversation?

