**Aims:**

To explore the effectiveness of an “Integrated Care for Older People (ICOPE)-Based Long-Term Care Intervention Program” compared to a control group and to assess participants’ perceptions of the program.

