Currently, practice-based projects centered around intrinsic capacity, at the heart of the ICOPE framework, are being gradually launched to improve the quality of care for older adults. These ICOPE practice projects have been implemented in multiple countries worldwide, including France (21) and South Korea (22), achieving significant results. In China, researchers such as Ma et al. (23) conducted a study on 976 middle-aged and older adults (aged 50–97) enrolled in the ICOPE-China project, using the ICOPE screening tool for intrinsic capacity assessments. The study found that 69.1% of participants showed a decline in intrinsic capacity, validating the tool’s effectiveness in identifying declines in the intrinsic capacity of older adults and providing valuable insights for the further development of older adult care in China. Overall, while domestic projects primarily focus on the initial screening of intrinsic capacity, there is still a lack of systematic research and practical application regarding the design and implementation of comprehensive care pathways and intervention programs, particularly for old patients with disabilities in nursing homes.

The main aim of this study is to explore the effects and the experiences of using “long-term care intervention program based on ICOPE for old patients with disabilities in nursing homes” in old patients with disabilities. An explanatory sequential design will be used, starting with a RCT investigating the impact of a long-term care intervention program on intrinsic ability (motor function, cognitive function, psychological function, sensory function, and nutrition) in a group of old patients with disabilities. Subsequently, qualitative surveys will be conducted to gain an in-depth understanding of participants’ subjective experiences of participating in this exergame intervention, in particular the benefits arising from the intervention as well as the influencing factors for participation, which will help understanding the mechanisms behind the therapeutic effects. This information will provide a basis for optimizing, refining, and promoting long-term care intervention program.

We hypothesis that participants in the long-term care intervention program group will experience an improvement of intrinsic ability, compared to those in the control group. Furthermore, we anticipate that these improvements will be maintained at 1-months follow-up.

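### Interview question 5 presupposes benefit, and no question asks explicitly about no change or worsening

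*Protocol article*

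**What the plan says.** The Abstract (Aims) gives the second aim of the study as assessing participants' "perceptions of the program", which favours neither direction. The Introduction describes the qualitative part as a study of subjective experience, then puts the weight on one side: "in particular the benefits arising from the intervention as well as the influencing factors for participation".

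Section 2.6.2 (Qualitative data collection) invites residents who have completed the 12-week program to focus groups and refers to Table 3 for a semi-structured outline of seven questions. Question 5 is "How do you think this care intervention program benefits you compared to traditional care models". The others include an open question on experience, "How did you feel and what were your experiences after participating in this care intervention program", and one on difficulties, "What challenges did you encounter during the implementation of this care intervention program".

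Section 2.8 (Statistical analysis) describes content analysis that builds upwards from open codes to subcategories and categories. Two researchers analyse the data and a third is consulted on disagreements.

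**The concern.** Question 5 takes benefit as given and asks the participant to describe it, with traditional care as the comparator. Someone who noticed no difference, or who felt worse, has to reject the premise before answering. The question has no neutral counterpart elsewhere in Table 3.

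This matters because the design is explanatory and sequential: the interviews follow the randomized comparison and are meant to help explain its result. If that result is null or mixed, the useful material is what residents thought did not change, or changed for the worse. The Conclusion also says that the qualitative findings will guide refinement of the intervention, which requires knowing which components did nothing or were unwelcome. A comparative question that prompts only for benefit is poorly suited to either purpose.

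**Working it through.** No arithmetic beyond a count applies, because the point rests on wording and on no rate, effect size or sample size. The check reads all seven questions of Table 3 against two tests. Does the question presuppose benefit? Does it leave room for a neutral or negative account?

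| Question | Content | Presupposes benefit | Room for neutral or negative account |
|---|---|---|---|
| 1 | Reasons for enrolling, ranked | No | Not about effects |
| 2 | "How did you feel and what were your experiences after participating in this care intervention program" | No | Yes, open in either direction |
| 3 | "What challenges did you encounter during the implementation of this care intervention program" | No | Yes, limited to difficulties in implementation |
| 4 | "Would you be willing to continue participating in this care program in the future" (also whether they would recommend it, with an explanation) | No | Yes, a refusal with reasons is possible |
| 5 | "How do you think this care intervention program benefits you compared to traditional care models" | Yes | Only by rejecting the premise |
| 6 | Future support wanted, and "Are there any areas that need improvement or further development" | No | Yes, invites criticism |
| 7 | "Is there anything else you would like to add to today’s conversation" | No | Yes, unrestricted |

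Count:
- Presupposes benefit: 1 of 7 (question 5).
- Leaves room for neutral or negative accounts: 5 of 7 (questions 2, 3, 4, 6 and 7).
- Concerns enrolment only: 1 of 7 (question 1). Together, 1 + 5 + 1 = 7.
- Asks explicitly about no change, worsening or unwanted effects: 0 of 7.
- Asks explicitly for effect relative to other care: 1 of 7, and it is question 5.

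The instrument can then be set beside the aims. The Abstract's aim is neutral. The Introduction names benefits and does not name absence of effect or harm. Question 5 follows the Introduction's emphasis, so the one-sidedness appears in both the stated purpose and the instrument.

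The remaining questions reduce the problem but do not remove it. Question 2 is neutral and comes before question 5, but it asks about feelings and experiences and not about what changed relative to other care. Questions 3, 4 and 6 concern difficulties, willingness to continue or recommend, and improvements. A resident could enjoy and recommend a program that changed nothing for them, and these answers would not show it.

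**The case against.** The strongest case on the other side is that question 5 is one item in a semi-structured outline. Residents can answer that they saw no benefit. Question 2 has already asked openly how they felt afterwards, and four further questions accept criticism or are unrestricted. The coding starts from open codes, so nothing excludes categories for no change or for negative experience. Section 2.6.1.8 has adverse events documented separately. Treatment effect is estimated from the scales and tests measured in both arms, not from the interviews. Probes may sit in a fuller interview guide that is not shown.

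Most of this stands, and it limits the point. A reader might infer that question 5 is the only question touching on effects, that participants have no way to report no change or harm, or that benefit themes will appear whatever residents experienced. The documents do not support those readings: question 2 alone contradicts the first two, and the inductive coding leaves the third unproven. Nor do they support saying that the interviews cannot inform the interpretation of a null trial, because questions 2, 3, 4 and 6 would still supply material on burden, barriers and acceptability.

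Residents' dependence on the home, and answering in front of peers, are concerns about the setting. They do not arise from the wording of question 5 and rewording would not change them, so they add no weight here.

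The defence does not answer the narrower point. The question printed in Table 3 starts from benefit, it is the only explicit comparison with other care, and no printed question balances it. Separate recording of adverse events captures untoward medical occurrences, not a resident's view that nothing changed.

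**Conclusion.** The point holds in a limited form. Question 5 is leading, it is the only question that asks explicitly about effect relative to other care, and no question asks explicitly about no change or worsening. The likely consequence is that benefit themes are over-represented in the qualitative findings, especially in the comparison with traditional care.

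The size cannot be derived from the document. It is one question in seven, and five others leave room for different answers. The primary outcome, the sample size and the group comparisons are not affected. The conclusion assumes that the question will be put as printed in Table 3. If the full interview guide already pairs it with a neutral probe, the effect would be smaller, but the printed wording would still be worth correcting. It is a small improvement in design, not a flaw that undermines the trial.

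**What to change.** Before the first focus group, replace question 5 with a two-sided form, for example: *Compared with your care before the program, what, if anything, is better, worse or no different for you? Please give examples.* This keeps the comparison with other care and still lets participants describe benefits.

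In the Introduction, change the emphasis on benefits to perceived effects, positive or negative, so that the purpose of the qualitative part matches the neutral aim in the Abstract.

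Leave the inductive coding in section 2.8 as it is. Preset categories for no change or worsening would conflict with that approach, and they are not needed once the question is neutral.

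The cost is one reworded question and one reworded phrase, plus any notification that the ethics committee requires (the document does not say whether it requires one). No extra interview time or data are needed. The timing matters because the effect of a leading prompt cannot be removed in the analysis once the focus groups have been held.

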### Quality control

2.7

Our team is an experienced group of researchers, consisting of senior experts and graduate students specializing in nursing. If there are complex clinical issues, the researchers in our team and professional experts will work together to find solutions. The researchers will deliver consistent and standardized training to all personnel involved in implementing the intervention. This group-based training will include demonstrations and assessments of scale usage to ensure that implementers are well-versed in both the content and application of the scales. Additionally, on-the-spot testing and questionnaire response collection will be carried out to guarantee the validity and accurate recall of the questionnaire data.

### Statistical analysis

2.8

For quantitative analysis, Epidata 3.1 (Epidata Association) will be used for double data entry and SPSS 26.0 (International Business Machines Corporation, IBM) will be used for data analysis and processing. Descriptive statistics will be used to describe participants’ characteristics and mental health outcomes. For continuous variables, the Shapiro–Wilk test (S-W test) will be used to assess normality. Depending on the results of the S-W test, the mean and standard deviation or the median and the interquartile range will be used for descriptive statistics. For categorical variables, frequencies and percentages will be reported. Independent samples *t*-tests, Mann–Whitney U tests and χ^2^ tests will be used to compare outcome results and baseline data. Paired sample t-tests or non-parametric rank sum tests will be used to compare the outcomes within the group. To analyze between-group differences, a two-independent sample t-test or a Mann–Whitney U rank sum test will be used. The changing trend of the outcome indicators of the study subjects will be measured between T_0_, T_1_, and T_2_; the inter-group factor will be the subgroup (intervention group and control group), the intra-group factor will be the measurement time point (T_0_, T_1_, and T_2_), and the interaction will be the group × time point. A generalized linear mixed model will be used for analysis. In addition, age, frailty status, and other relevant variables will be included as covariates, depending on data availability and implementation feasibility, to control for their potential confounding effects. The significance level of all the above statistical tests will be set at *p* ≤ 0.05, indicating a significant statistical difference.

Regarding qualitative data analysis, one researcher will transcribe the interview audio recordings within 24 h after the interview and enter the transcriptions into Nvivo 12 (QSR International Pty Ltd), and another researcher will check these transcriptions. Nvivo 12 will be used for coding, and data will be analyzed and collected in parallel. Qualitative content analysis will be applied to the data collected (40). This method is an objective, systematic and quantitative research method applied to text content, which is based on the generation of explicit and descriptive content categories and the generation implicit and explanatory content themes. First, researchers will read the transcripts multiple times to get a sense of the data as a whole. Secondly, a series of open codes will be identified, and similar and related codes will be classified into subcategories. These subcategories will be then abstracted into generic categories, and finally, general categories will be summarized into main categories. Two researchers will analyze the data at the same time and compare their coding frameworks. If there is a disagreement, a third researcher will be consulted until an agreement is reached to improve the quality of the analysis.

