**Methods:**

This mixed-methods study will employ an explanatory sequential design, starting with a quantitative evaluation using a randomized controlled trial (RCT), followed by a supplementary qualitative study. The old patients with disabilities will be randomly allocated in a 1:1 ratio into the intervention group or the control group. The old patients with disabilities in the intervention group will participate in a 12-week “ICOPE-Based Long-Term Care Intervention Program,” and in the control group will maintain their routine life and standard care practices. Participant outcomes in both conditions will be assessed at pre-intervention (T_0_, week 0), post-intervention (T_1_, week 12), and 1 month after the intervention (T_2_, week 16), and a generalized linear mixed model will be used for analysis. The primary outcome is the change in intrinsic capacity, with the significance of the mean difference assessed to determine the intervention effect. In the qualitative part of this study, interviews will be conducted with old patients with disabilities from the intervention group at T_1_ to explore their experiences of receiving the intervention, and content analysis will be applied to the data collected.

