### Sample size and power calculations

2.2

In quantitative research, this study will use a completely randomized design for sample size estimation. A repeated measures ANOVA *F*-test in G*Power 3.1 will assess the main effect of the within-between interaction. Parameters will be set as follows: effect size = 0.25, *α* = 0.05, 1-*β* = 0.90. The correlation among the three repeated measures was set to *r* = 0. Note that this reflects a conservative approximation and any correlation larger than *r* = 0 would have reduced the required amounts of participants. Software calculations will determine a required 70 participants (35 per group). Accounting for a 20% attrition rate, the final sample size will be 42 per group, totaling 84 participants.

In qualitative research, purposive sampling will be used to select old patients with disabilities in nursing homes who have completed the 12-week intervention. Recruitment, interviews, and data analysis will be conducted sequentially in an iterative process until data saturation is reached, determining the final sample size (29).

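### Section 2.8 gives the between-group comparison to a t-test or Mann-Whitney test and also to a mixed model, and no deciding contrast or time point is fixed

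*Protocol article*

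**What the plan says.** Three places in the protocol article bear on how the primary outcome decides the trial.

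- **Abstract, Methods:** "The primary outcome is the change in intrinsic capacity, with the significance of the mean difference assessed to determine the intervention effect". The mixed model is the only analysis method the abstract names for the quantitative outcomes. It ties the mean difference neither to T1 or T2 nor to a term of that model.
- **Section 2.2, Sample size:** "A repeated measures ANOVA *F*-test in G*Power 3.1 will assess the main effect of the within-between interaction", with "effect size = 0.25, *α* = 0.05, 1-*β* = 0.90" and "The correlation among the three repeated measures was set to *r* = 0". The result is 70 participants, 35 per group.
- **Section 2.8, Statistical analysis:** "To analyze between-group differences, a two-independent sample t-test or a Mann–Whitney U rank sum test will be used". After describing group, time and group × time as factors, it adds: "A generalized linear mixed model will be used for analysis". For change within an arm: "Paired sample t-tests or non-parametric rank sum tests will be used to compare the outcomes within the group". All tests share the threshold p ≤ 0.05. The covariates are left open, depending on what proves available and feasible.

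Section 2.6.1 schedules the outcome measures at T0, T1 and T2 without ranking the follow-up visits. The hypothesis at the end of the Introduction expects improvement relative to control, and then that it lasts to one month.

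**The concern.** The plan offers several between-group results for the same outcome: a t-test or Mann-Whitney test at each of two follow-up times, on the score or on its change, and a mixed model with its own interaction and contrasts. These can disagree. The document does not say which one is the trial's answer, and the sentence that deals expressly with between-group differences names a method other than the one in the abstract and the one behind the sample size.

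This is more than detail left to a fuller analysis plan. The article states the competing analyses side by side, at one threshold and with no order among them. If the deciding result can be picked after the data are seen, the 5% error rate no longer describes the trial's main claim, and the reported effect may not be the declared mean difference. Blinding the data analysts (section 2.4) does not prevent selection among p-values.

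**Working it through.** **1. The plan's own figure.** Inputs from section 2.2: f = 0.25, α = 0.05, power 0.90, k = 2 groups, m = 3 measures, r = 0. For the group × time interaction under sphericity:

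- λ = f² × N × m / (1 − r); df1 = (k − 1)(m − 1) = 2; df2 = (N − k)(m − 1).
- N = 68: λ = 0.0625 × 68 × 3 = 12.75, df2 = 132, power 0.895.
- N = 70: λ = 0.0625 × 70 × 3 = 13.125, df2 = 136, power 0.904.

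So N = 70 reproduces, for the interaction test. The article gives no mean difference or standard deviation, so the power of a single contrast at T1 cannot be derived from it.

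**2. A rough guide.** Two independent tests at 0.05 give 1 − 0.95² = 9.75%. Four give 1 − 0.95⁴ = 18.5%. The tests here are correlated, so simulation is needed.

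**3. Simulation with no true effect.** 10,000 trials, 35 per arm, two-sided p ≤ 0.05. The article gives no sidedness and no outcome distribution, and its r = 0 is a planning value. The assumptions are therefore a correlation among T0, T1 and T2 of 0, 0.5 or 0.7, and an outcome that is either normal or a six-level ordinal score. The interaction F-test stands in for the mixed model. The ranges span all six settings.

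| Results that may count as success | Chance of at least one p ≤ 0.05 |
|---|---|
| Interaction test alone | 4.7–5.1% |
| t-test on the score at T1 or T2 | 8.5–9.8% |
| t-test on the change at T1 or T2 | 8.8–9.3% |
| Change at T1 or T2, or the interaction | 9.5–10.1% |
| t-test or Mann-Whitney on the score at T1 or T2 | 9.5–11.5% |
| The row above, plus the interaction | 12.4–14.4% |
| The row above, plus t-tests on change | 16.0–18.5% |

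The second time point alone nearly doubles the error rate. Mann-Whitney as an alternative adds little (8.5–9.8% becomes 9.5–11.5%). The choice between score and change adds more. Within-group tests are left out of every row, and the open covariate choice was not simulated.

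**The case against.** The strongest reply is that the intended analysis can be recovered. The abstract names only the mixed model, the sample size rests on the group × time interaction, and section 2.8 sets out those same terms. The hypothesis that improvement is maintained at one month suggests that T1 comes first. This stands as a reading of intent, and it means that this is not an open contest among equals. It does not settle the matter. Section 2.8 still gives between-group differences to other tests, and even within the mixed model the deciding quantity could be the interaction, the T1 contrast or the T2 contrast.

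Four stronger readings are tempting, and the text does not support them.

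- **Shapiro-Wilk as a gate.** A reader might infer from "Depending on the results of the S-W test, the mean and standard deviation or the median and the interquartile range will be used" that a failed normality test sends the primary outcome to Mann-Whitney. The sentence goes on to limit itself to descriptive statistics. No rule for choosing between the t-test and Mann-Whitney is written.
- **The 0–5 score as the declared primary measure.** The ICOPE total in section 2.6.1.1 is the likeliest candidate. The abstract says only intrinsic capacity, and Table 2 lists that tool beside six other instruments.
- **Success from one arm.** A significant change in the intervention arm alone is not a stated criterion; the hypothesis is comparative.
- **An invalid paired test.** The rank sum wording for within-group comparisons is probably loose naming of a paired rank test, since it stands next to the paired t-test.

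**Conclusion.** The concern holds in this form: section 2.8 states more than one between-group analysis at the same threshold, and no part of the article fixes the deciding contrast or time point. The error rate for a claim of success is about 9 to 10% if T1 or T2 may count. It is about 16 to 18% if post scores, change scores and the other listed between-group tests may count. One designated test gives about 5%. These rates assume 35 analysed per arm, correlations of 0 to 0.7, two-sided tests and normal or six-level ordinal outcomes. They show what the wording permits and do not predict what the sponsor will do. The sample size of 70 is correctly computed for the interaction test and supports no other choice of primary test without a further calculation.

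**What to change.** In section 2.8, name one primary analysis. A workable choice is the between-group mean difference in change in the ICOPE intrinsic capacity score from T0 to T1 (week 12), estimated from the mixed model with a 95% confidence interval, in all randomised participants and with covariates fixed in advance. State that the ICOPE score is the primary measure.

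Make T2 and the domain measures secondary, and the t-test and Mann-Whitney comparisons supportive. Report within-group changes descriptively; if a paired rank test is shown, call it signed-rank.

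Then align the abstract with sections 2.2 and 2.8. Either designate the group × time interaction, for which N = 70 holds, or restate the power for the T1 contrast with an assumed difference and standard deviation.

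The cost is mostly wording. The sponsor gives up the alternative tests as evidence of success, and the stated power may have to be restated if the T1 contrast is chosen.
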